### Standard treatment

The control group consists of eligible patients from the subcohort who were not randomly selected to receive an offer of the sponge intervention. During surgery, the control patients are positioned in the Trendelenburg position, which is standard care during laparoscopic colorectal surgery. The surgeon will decide the angle of the Trendelenburg without a pre-specified angle range. Aesthetical, surgical, and pre- and post-supportive care other than the positioning of the patient are not prescribed by this study protocol and are carried out according to the standards used in the hospital.

### Primary outcome

The primary endpoint of this study is postoperative hospital stay, defined as days from surgery until discharge. Discharge needs to be approved by a checklist confirmed by the attending physician. The checklist includes the following items: absence of fever (temperature below 38.5 °C); adequate pain management (VAS score below 4); absence of leukocytosis; passing stool (anally or via stoma); resumption of normal food intake (no nausea or vomiting); absence of an active, unstable and untreated cardiac, pulmonary or surgical complication; and presence of a supportive person at home at the time of discharge [16, 17].

### Secondary outcomes

Secondary endpoints are duration of surgery (minutes), blood-loss (mL), fluid balance (L), body temperature on arrival at the recovery room, oxygen therapy at discharge of the recovery room and postoperative complications (until 30 days after primary surgery).

Pulmonary complications are defined as respiratory failure, requiring mechanical ventilation; atelectasis, pleural effusion, or pneumothorax, as diagnosed on chest radiographs; or pneumonia, based on clinical, laboratory, and imaging findings combined with initiation of antibiotic therapy. Cardiac complications are reported as symptoms of myocardial ischemia and cardiac events, including acute myocardial infarction, congestive cardiac failure, new-onset or rapid atrial fibrillation, major arrhythmia, and cardiac arrest. Surgical complications are reported as symptoms of surgical site infection, anastomotic leakage, postoperative bleeding, or ileal and early stoma-related complications (that is, ischemia, stoma retraction, or small bowel obstruction). All endpoints will be captured from patients’ medical file, operation, and anesthesia records.

### Data collection

Clinical data are being captured from the patients’ electronic medical files and will be collected in an electronic database encompassing data of all cohort participants. In this database, variables are registered under a unique study number provided to each cohort participant. For patients in the SPONGE trial, additional clinical information, that is, duration of surgery, blood loss, fluid balance, postoperative body temperature, and oxygen therapy, will be collected from electronic medical files. Only the research office of the Imaging Division, University Medical Center Utrecht, possesses the key to link study numbers back to patient identifiers. At baseline, data will be collected on demographics, body mass index, co-morbidities, tumor characteristics, neoadjuvant therapy, ASA classification, type of anesthesia, and surgical procedure.

### Sample size

In the previously mentioned pilot study, the hospital stay in the in the Trendelenburg group was 7.0 days compared to 5.4 days in the sponge-assisted surgery group, with a standard deviation of 2.04 [10]. To calculate a sample size, we used a two-sided test with a type I error of 5 % and power of 80 %. We assumed a difference in duration of hospital stay of 1 day to be clinically relevant (5 days in the sponge group versus 6 days in the control group). Based on a refusal rate of 10 % in the intervention arm, a sample size of at least 82 patients per arm is needed to confirm this hypothesis. Because hospital stay generally does not have a Gaussian distribution, we decided to add 15 % in order to adjust the sample size for analysis with nonparametric tests [18]. Our final sample size was calculated to be 98 patients per arm.

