## Background

Colorectal cancer is the fourth most common cause of cancer worldwide with the highest incidence in developed countries [1]. Surgery is still the cornerstone of curative colorectal cancer treatment. In the Netherlands, more than half of the colorectal resections is performed laparoscopically [2]. In laparoscopic colorectal surgery, a clear view on the operating field without disturbance of the small intestine in the pelvic region is essential. To achieve this, patients are positioned in a head down (Trendelenburg) position, having gravity retract the intestines away from the pelvic region to obtain a clear working field [3]. The Trendelenburg position is associated with hemodynamic instability due to the increased intrathoracic and intracranial pressure [4–6]. This may complicate anesthetic control and could potentially cause postoperative airway obstruction due to laryngeal edema, and a decrease in postoperative lung function [7–9]. Nevertheless, the effects of the Trendelenburg position on postoperative outcomes, for example, cardiac and pulmonary complications and hospital stay, are still unclear because alternatives for the Trendelenburg position have not been available so far.

Recently, the Endoractor™ (CE Kawamoto Corporation, Osaka, Japan) retractor sponge has been introduced to keep the small intestine aside and create a proper view during laparoscopic pelvic surgery while the patient is in a horizontal position. The initial Dutch experience with the retractor sponge comes from a nonrandomized matched pilot study in which 45 patients underwent sponge-assisted operations and 45 control patients were operated on while in the Trendelenburg position [10]. Patients who underwent sponge-assisted surgery had a shorter hospital stay compared to those in the Trendelenburg position (5.4 and 7 days, respectively, *P* = 0.041). Fewer cardiac complications were observed in the sponge-assisted surgery group compared to the Trendelenburg group, although this difference was not significant (one patient with heart failure versus three patients with heart failure and one patient with myocardial infarction, respectively). These results seem promising; however, confirmation with larger numbers in a randomized setting is required.

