### Statistical analysis

Data will be analyzed according to the intention-to-treat principle. Differences in continuous outcomes will be tested using independent samples t-tests or nonparametric equivalents, depending on the distribution. Chi squared tests (or Fishers Exact tests) will be used to test differences in categorical variables. Adjusted analyses will be performed in case of unbalanced randomization between the intervention and control arm. A *P* value of 0.05 is considered significant. Statistical analyses will be performed using Statistical Package for Social Sciences (SPSS) software (IBM SPSS Statistics for Windows, Armonk, NY: IBM Corp.).

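### The SD of 2.04 behind the 82 per arm does not fit the same pilot's P value if it applies to both groups, so the stated 80% power is not supported until the figure is verified

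*Protocol article*

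**What the plan says.** The Sample size section of the protocol article takes its variability from the non-randomised pilot, where stay was 7.0 days in the Trendelenburg group "compared to 5.4 days in the sponge-assisted surgery group, with a standard deviation of 2.04". It then sets the design values: "we used a two-sided test with a type I error of 5 % and power of 80" per cent; "We assumed a difference in duration of hospital stay of 1 day to be clinically relevant" (5 versus 6 days); and "Based on a refusal rate of 10 % in the intervention arm". From these it states that "a sample size of at least 82 patients per arm is needed to confirm this hypothesis". A further 15% is added for nonparametric testing, and the section ends at 98 per arm; the Abstract gives 94.

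The Background describes the same pilot, with 45 patients in each group: "Patients who underwent sponge-assisted surgery had a shorter hospital stay compared to those in the Trendelenburg position (5.4 and 7 days, respectively", with P = 0.041. Neither section names the test behind that P value, says whether 5.4 and 7 are means or medians, or says whether 2.04 is a pooled SD or one group's SD.

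The Statistical analysis section states "Data will be analyzed according to the intention-to-treat principle" and allows a t-test or a nonparametric equivalent, depending on the distribution.

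**The concern.** The SD is the only variability input to the sample size, and required n grows with its square. The article prints enough about the pilot (group sizes, both averages, the P value) to test whether 2.04 is plausible as a common SD, and it does not pass.

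If the true spread is well above 2.04, none of 82, 94 or 98 per arm gives 80% power for the 1-day difference that the plan calls clinically relevant. A non-significant primary result could then be read as evidence against a relevant benefit when the trial had a much lower chance of detecting one than the article states.

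**Working it through.** **Inputs.** From Sample size: two-sided alpha 0.05, power 80%, difference 1 day, SD 2.04, refusal 10%. From Random selection: 1:1 allocation. From Statistical analysis: intention to treat. From Background: pilot of 45 versus 45, 7 versus 5.4 days, P = 0.041.

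**1. Reproducing 82.** With 10% refusal under intention to treat, the difference is diluted to 1 × 0.9 = 0.9 day. The normal formula gives n = 2 × [2.04 × (1.960 + 0.842) / 0.9]² = 80.65, that is 81. The t-based solution is 81.6, that is 82, where power is 80.2%. So the plan's figure is right for its inputs, and refusal is treated as dilution, not as dropout (66/0.9 would give only 74).

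**2. Testing 2.04 against the pilot result, if it applies to both groups.**
- SE = 2.04 × √(2/45) = 0.430
- t = (7.0 − 5.4)/0.430 = 3.72 on 88 df, so P = 0.00035, not 0.041

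**3. The common SD that P = 0.041 requires.**
- t for two-sided P = 0.041 on 88 df is 2.074, so SE = 1.6/2.074 = 0.7715
- SD = 0.7715/√(2/45) = 3.66
- Allowing for rounding of the averages and of P, the range is 3.42 to 3.90

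**4. Does matching explain it?** A paired t-test on 45 pairs needs t = 2.105, so the SD of the differences is 1.6 × √45/2.105 = 5.10. With zero within-pair correlation the SD per group is 5.10/√2 = 3.60; with correlation 0.3 it is 4.31. Positive correlation, the usual result of matching, widens the gap.

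**5. Does a one-group SD explain it?** If 2.04 belongs to the sponge group only, the control variance is 0.7715² × 45 − 2.04² = 26.78 − 4.16 = 22.62, an SD of about 4.76. Both printed figures can then be true. The root-mean-square SD is √[(4.16 + 22.62)/2] = 3.66, so 2.04 would still be the wrong input for a two-arm calculation.

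**6. Does a rank test explain it?** In simulated pilots with means 7 and 5.4, SD 2.04 in both groups and stays rounded to days, the median rank-test P was about 0.0002 (lognormal) to 0.0004 (gamma), and only 3% to 5% of samples reached 0.041. With SDs of 2.04 and 4.76 (lognormal), the median P was about 0.21 and about 78% reached 0.041. A rank test is thus an unlikely explanation under a common SD, but it cannot be excluded in general.

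**7. Consequence for power.** t-test, 0.9-day difference (noncentral t):

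| SD | 82 per arm | 94 per arm | 98 per arm |
|---|---|---|---|
| 2.04 | 80% | 85% | 87% |
| 2.5 | 63% | 69% | 71% |
| 3.0 | 48% | 53% | 55% |
| 3.66 | 35% | 39% | 40% |

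At SD 3.66 with 98 per arm, simulated rank-test power was about 53% (gamma) to 66% (lognormal). The difference detectable with 80% power by t-test is about 2.80 × 3.66 × √(2/98) = 1.5 days under intention to treat, or 1.5/0.9, about 1.6 days, in those who accept the sponge.

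**The case against.** A reader might infer that the SD and the P value cannot both be right. The documents do not support that. The SD follows directly after the sponge group's 5.4 days and is never called pooled, so it may describe that group alone, and a control SD near 4.76 would then reconcile the figures. The pilot's test is not named, the averages are not labelled as means or medians, and the Sample size section itself says that stay is generally not Gaussian. A rank test therefore cannot be ruled out as the source of P = 0.041.

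A reader might also infer that the trial's power is simply about 40%. That is too strong as well. It assumes a t-test, a correct P value, and a trial SD equal to the back-calculated pilot value. The plan allows a rank test, which with skewed stays does better. The planning scenario (6 versus 5 days) is not the pilot's (7 versus 5.4), and discharge in the trial follows a checklist, so the pilot spread need not carry over.

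These objections remove the certainty and the single power figure. They do not restore the 80%: the one-group reading leaves the root-mean-square SD at 3.66, and the rank-test figures at that SD remain below 80%. Only one outcome leaves the sample size intact: 2.04 really is a common SD and the P value is misprinted or comes from an unusual sample. The article gives no means of telling.

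**Conclusion.** The concern holds as an unreconciled input, not as an error of calculation: 82 follows from the stated values. If it applies to both groups, an SD of 2.04 does not fit P = 0.041 in 45 versus 45 patients; a t-type comparison of means needs about 3.66. If it applies to the sponge group only, it was used for both arms when the average spread was still about 3.66. Either way, 80% power is unsupported as written.

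If the pilot P value is right and the trial's SD resembles the pilot's, power at 98 per arm for the 1-day effect with 10% refusal is about 40% by t-test and about 53% to 66% by rank test, the latter under assumed gamma or lognormal stays. At intermediate SDs the t-test loss is smaller (71% at 2.5, 55% at 3.0). The mismatch itself is firm; the size of the power loss is conditional.

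**What to change.** Go back to the pilot data and establish two things: what 2.04 represents (common SD, one group's SD, or another statistic) and whether P = 0.041 is correct, and from which test. One prompt for that check: the two-sided normal deviate for P = 0.041 is also 2.04, which may be coincidence and proves nothing by itself. Then correct the wrong figure, or stop applying a one-group SD to both arms, and label the SD and the averages in the Sample size section.

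If the appropriate SD is above 2.04, restate power at the planned size over SDs from 2.0 to 3.7, for both the t-test and the rank test, with the distribution assumed for the latter, and give the difference detectable at 80% power (about 1.5 days under intention to treat at SD 3.66 and 98 per arm, by t-test). If 2.04 is confirmed as the common SD, the power statement can stay and the P value in the Background needs correcting or explaining.

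The cost is one rewritten paragraph and possibly a less favourable stated power. The correction does not require added patients.

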**Methods/design:**

The SPONGE trial is a monocenter study and follows the cohort multiple randomized controlled trial (cmRCT) design. It will be conducted within a multicenter prospective observational cohort of colorectal cancer patients of all stages, for whom longitudinal clinical data and patient-reported outcomes are collected. Patients within the cohort, who will undergo laparoscopic surgery for distal colon or rectal cancer, are eligible for inclusion and form a subcohort. From this subcohort, a 1:1 random sample will be offered to undergo surgery with the use of the retractor sponge. Patients from the subcohort who are not selected will undergo standard treatment, that is, surgery in the Trendelenburg position. The primary endpoint is the duration of the postoperative hospital stay. Secondary outcomes are duration of surgery; intraoperative blood loss and fluid balance; and postoperative body temperature, oxygenation and complications. Both arms require 94 patients.

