### Random selection

Participants who meet the inclusion criteria of the SPONGE trial form a subcohort of eligible patients (Fig. 1). From this subcohort, patients are randomly selected on a 1:1 basis. Randomly selected patients are offered sponge-assisted surgery. Stratified randomization is performed to take into account participation in other ongoing trials within the cohort, of which the (secondary) endpoints may interfere with endpoints of the SPONGE trial. At this moment, patients are stratified according to whether they received boost radiotherapy in the context of the RECTAL BOOST study, which is running as a cmRCT within the cohort (ClinicalTrials.gov: NCT01951521) [14]. In this trial, a randomly selected group of patients with locally advanced rectal cancer is offered an additional radiation boost prior to standard neoadjuvant chemoradiation. Stratified randomization, using dedicated software, takes place at the Imaging Division University Medical Center Utrecht.

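### The abstract sets 94 patients per arm and the sample-size section sets 98; adding the stated 15 % to 82 gives 94.3, so 98 does not reproduce as worded

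*Protocol article*

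**What the plan says.** The final number per arm appears twice in the protocol article, with different values.

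- Abstract, Methods/design: "Both arms require 94 patients".
- Methods/design, Sample size: "Our final sample size was calculated to be 98 patients per arm".

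The Sample size section also gives the route to its figure. On error rates it says "we used a two-sided test with a type I error of 5 % and power of 80" %. The difference to be detected is 1 day of hospital stay (5 versus 6 days), and the spread comes from the pilot study, "with a standard deviation of 2.04". The intermediate result is "Based on a refusal rate of 10 % in the intervention arm, a sample size of at least 82 patients per arm is needed". The last step is an allowance for skewed length-of-stay data: "we decided to add 15 % in order to adjust the sample size for analysis with nonparametric tests". Allocation is equal; under Random selection, "From this subcohort, patients are randomly selected on a 1:1 basis".

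**The concern.** Two current statements give different values for the same quantity, and nothing in the article says which one governs. This is not a difference between current text and an amendment log.

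The section that derives the number is also the one whose last step does not follow from its own words. A reader who takes 82 and adds 15 % arrives near the abstract's figure, not at the one the section prints.

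At stake is a clear, checkable enrolment target. The trial is unblinded and, according to Trial status, already enrolling. A later reader who compares the number recruited with the number planned should find one planned number and be able to retrace it.

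**Working it through.** **Inputs** (Sample size section unless noted): SD 2.04 days; difference 1 day; two-sided alpha 0.05; power 0.80; refusal 10 % in the intervention arm; nonparametric allowance 15 %; 1:1 allocation (Random selection).

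**Step 1. Base size per arm.**
Normal approximation: n = 2 × [SD × (z₀.₉₇₅ + z₀.₈₀) / difference]² = 2 × [2.04 × (1.960 + 0.842) / 1]² = 65.3, rounded up to 66.
Two-sample t-test with d = 1/2.04: n = 66.3, rounded up to 67.

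**Step 2. Refusal.** Analysis is by intention to treat. If the 10 % who refuse have the control-group mean, the difference shrinks to 0.9 × 1 = 0.9 day and n grows by 1/0.9² = 1/0.81.
- From 66: 66/0.81 = 81.5, rounded up to 82.
- From the unrounded t-test value: 66.3/0.81 = 81.9, rounded up to 82.
- From 67: 67/0.81 = 82.7, rounded up to 83.

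The printed 82 is reproduced. Simple division by 0.9 would give only 66/0.9 = 73.3, so the authors evidently used the dilution formula.

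**Step 3. The 15 % allowance.**

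| Reading of the 15 % | From the printed 82 | From 83 (not printed) |
|---|---|---|
| Add 15 % (× 1.15) | 94.3: 94 to nearest, 95 rounded up | 95.4: 95 to nearest, 96 rounded up |
| Divide by 0.85 | 96.5: 97 rounded up | 97.6: 98 rounded up |

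Working backwards, 98 by multiplication needs a base of 98/1.15 = 85.2 per arm, or an inflation of 98/82 = 1.195 (19.5 %). Neither is stated. Division by 0.85 adds 1/0.85 − 1 = 17.6 %, which is not the literal sense of adding 15 %.

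**Step 4. Power at each target** (difference 0.9 day, SD 2.04, two-sided 5 %). The effective n is the target divided by 1.15, or multiplied by 0.85.

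| Per arm | No allowance, t-test | n/1.15, t-test (normal) | n × 0.85, t-test (normal) |
|---|---|---|---|
| 94 | 85.3 % | 80.1 % (80.5 %) | 79.2 % (79.6 %) |
| 98 | 86.7 % | 81.7 % (82.1 %) | 80.8 % (81.3 %) |

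**Size of the gap.** 98 − 94 = 4 per arm; 196 − 188 = 8 in total, about 4 %.

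**The case against.** The best defence is that 98 can be explained. If the t-test base of 67 is rounded up at each step and the 15 % is applied as division by 0.85, the sequence 67, 83, 98 uses only the stated inputs. This has some force: it would be wrong to say that 98 has no possible derivation. But the route passes through 83 where the article prints 82, and it divides where the article says it adds. From the printed 82, division gives 97. So 98 has a plausible origin, but not one that the text states.

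Three stronger conclusions are tempting, and the article does not support them.

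- **That 94 is the one correct figure.** The intermediate result is worded as a minimum, so rounding up is the natural convention, and 94.3 rounds up to 95. Under that convention neither printed total follows exactly.
- **That the trial is underpowered or has no valid size.** Power is about 80 % or slightly more at both targets. It falls to 79 % only at 94 and only under the division reading.
- **That investigators can choose the stopping point after the fact.** The article describes no interim look. It reports ethics approval of a study protocol on 5 December 2014, before the November 2015 start. That protocol is not shown, and it may fix a single number.

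It can also be said that the body of an article outranks its abstract, and the Sample size section does call its figure final. That tells a reader which number the authors probably meant. It does not remove the difficulty that this is the number that fails to reproduce as worded.

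**Conclusion.** The inconsistency is real but modest. The article gives two per-arm targets, 94 and 98, and does not reconcile them. Its own steps lead to 82 and then to 94.3, so 98 does not follow from the words as printed.

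The consequence is an ambiguous enrolment target of 188 or 196 patients and about 1.6 percentage points of t-test power between the two. Hypothesis, endpoint and analysis are untouched.

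This rests on two readings: that the refusal allowance is intention-to-treat dilution, which the reproduced 82 supports, and that the 15 % is meant literally as an addition. If it was applied as division by 0.85, 98 is nearly explained, but the two targets then lie on either side of the planned 80 % (79.2 % and 80.8 % by t-test). That is a further reason to state how it was applied.

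**What to change.** Print one per-arm target in both the abstract and the Sample size section, by one of two routes:

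- **95 per arm** (190 in total), from 82 × 1.15 = 94.3 rounded up; or
- **98 per arm** (196 in total), with the derivation written out: the base before inflation, whether the 15 % is a multiplication by 1.15 or a division by 0.85, any further allowance, and the rounding.

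Name that figure as the recruitment target and check it against the ethics-approved protocol. The cost is a wording correction in two places, with no design change.
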